## Secondary study parameters/endpoints

- To identify cutaneous hyperesthesia or hypoesthesia by:
  - - Physical exam (in collaboration with a pain specialist)
    - Pain Catastrophizing Scale questionnaire ^[[12]](#endnote-12)^

A validated questionnaire about pain catastrophizing (a tendency to misinterpret and exaggerate situations that may be threatening) in 3 subscales: magnification, rumination, and helplessness

- - - Mc Gill Pain Questionnaire, Dutch language version^[[13]](#endnote-13)^

A validated questionnaire about chronic pain, which measures the different qualities of the subjective pain experience

- - - Postoperative ultrasound after 6 weeks with repeat measurements of intercostal and subcostal nerves
- To correlate postoperative dullness, neuropathy, pain or muscle weakness to subcostal nerve damage on ultrasound.

### Baseline parameters

- Date of surgery
- Sex
- Age
- Height
- Weight
- BMI
- Comorbidity
- Medications
- Side of adrenalectomy
- Indication of surgery
- Pressure of pneumo-retroperitoneum
- Duration of surgery
- Intraoperative analgesics
- Postoperative analgesics
- Complications related to PRA
- Length of hospital stay after PRA

## Study procedures

All patients will be approached at the outpatient clinic by [name] (researcher) after the decision is made to perform PRA, explaining the study and its procedures. They will be given additional written information including a consent form. If the patient gives informed consent and has no exclusion criteria, he/she will be included in the trial.

Preoperatively:

1. Preoperative questionnaires: (cross-sectional), duration: in total ± 15 minutes.

- Mc Gill Pain questionnaire (Dutch Language version) (5 minutes)
- Hypoesthesia questionnaire (5 minutes)
- Pain Catastrophizing Scale questionnaire (5 minutes)
- Physical examination (5 minutes)

Intraoperatively:

1. After positioning in jack-knife position, an ultrasound is performed by a clinical neurophysiology research technician with measurement of the intercostal / subcostal nerve (see scan-protocol below). Nerve locations are captured with photography. Since the objective of this explorative study is to identify nerve damage after trocar placement and surgery and to see if the current surgical technique needs improving, surgeon is blinded for the results of preoperative ultrasound measurements to reduce bias.

2. PRA will be performed using the normal, clinically and scientifically validated surgical technique.

3. After wound closure a tegaderm foil is applied over the wound. Then repeat measurement of intercostal / subcostal nerve is performed to assess nerve damage / oedema. The distance of subcostal nerves to trocar locations (shortest distance to nerve, in mm) is measured. Again this is captured with photography. Surgeon is blinded for these results as well to prevent bias in future procedures. After this a sterile drape is applied.

Postoperatively after 6 weeks:

1. Postoperative questionnaires: (cross sectional), duration: in total ± 15 minutes.

- Mc Gill Pain questionnaire (Dutch Language version) (5 minutes)
- Hypoesthesia questionnaire (5 minutes)

2. Physical exam by clinical neurophysiology research technician to evaluate dermatomas and subtle neurological injury

3. Repeat ultrasound measurement of intercostal / subcostal nerve to assess nerve damage if neurological injury is present.

Ultrasound protocol:

- Equipment: Sonoside Xporte ultrasound system with linear 5-16Mhz probe, using preset “zenuwecho S”.

- Positioning of patient: jack-knife (see image below)

[figure not shown]

- Scan-protocol:

- Depth: 6cm, gain 60-70%

- Transversal position of probe, midaxillary line. Locating 10^th^, 11^th^ and 12^th^ rib.

- Locating tip 12^th^ rib, locating nerve latero-caudally (power doppler to verify adjacent blood vessel)

- Cross sectional area (CSA) measurement of subcostal nerve, marking the position on skin

- Following lateral / medial cutaneous nerve branches in surgical area, capturing and CSA measurement of abnormalities with note of localization with respect to midaxillary (vertical) and umbilical (horizontal) lines

Data management:

Given informed consent, filled out questionnaires, medical data extracted from electronic patient records are analyzed by [name] and stored in separate folders. Only [name] and HL (primary investigator) have insight in these data. Other authors in this study can view the data upon request. The data will be stored for 15 years.

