In literature neuropathy is a common symptom after surgery. The affected nerve and resulting neuropathy, muscle weakness or pain depends on different types of surgery. Common mechanisms of surgery related nerve injuries include compression, entrapment/angulation, direct trauma including crushing or laceration injuries, and indirect trauma^[[7]](#endnote-7)^. Walz et al. shows a prevalence of chronic hypoesthesia of the abdominal wall of 8% after retroperitoneoscopic adrenalectomy for primary adrenal tumors, although because of the retrospective character of this study there could be a selection bias in these data^[[8]](#endnote-8)^. After percutaneous nephrolithotomy sensory neurological complications were reported in 12% of the patients, with a significant correlation between prolonged duration of surgery and the incidence of sensory complications^[[9]](#endnote-9)^. After living-donor nephrectomies the incidence of chronic postoperative pain was 5.7%, resulting in a significant lower quality of life^[[10]](#endnote-10)^. Depending on the type of surgery, chronic postsurgical pain is often neuropathic pain (on average 30% of cases with a range from 6% to 54% and more)^[[11]](#endnote-11)^. Pain including such a neuropathic component is usually more severe than nociceptive pain and often affects the quality of life more adversely.

Since the introduction of PRA, several modifications and refinements of the surgical technique have been implemented to improve patients’ recovery and lower the number of intra- and postoperative complications. Because nerve damage can result in significant complaints and this subsequently can result in a lower quality of life, we aim to see if the surgical technique can be further improved by locating this nerve and prevent damage. Therefore, we plan to investigate if the intercostal and subcostal nerves can be visualized pre- and postoperatively by ultrasound, what the distance is of the trocar positions to this nerve, and if we can visualise nerve injuries by ultrasound (direct lesions, oedema). Furthermore, after 6 weeks we want to repeat the ultrasound to see if nerve damage can be visualized at a later stage. If so, we aim to see in the future if the surgical technique can be altered to prevent this.

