# OBJECTIVES

*Primary Objective:* to investigate if the subcostal nerve can be visualized perioperatively in patients undergoing retroperitoneoscopic adrenalectomy, to measure distance from the trocar incisions and to assess nerve damage directly postoperative.

*Secondary Objective(s):*

To identify postoperative cutaneous hyperesthesia or hypoesthesia and to correlate postoperative dullness, neuropathy, pain or muscle weakness to subcostal nerve damage on ultrasound, after 6 weeks.

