# STUDY DESIGN

A explorative single-center prospective cohort study (n=25) at the Radboud University Medical Centre in Nijmegen.

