## Benefits and risks assessment

There are no risks. The burden for the patients is small, due to a longer narcosis (estimated 10 minutes) and extra examinations (ultrasound, physical examination, questionnaire) after 6 weeks (estimated 20 minutes).

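### The protocol contradicts itself on who has the 6-week ultrasound; if only patients with neurological injury are scanned, injury cannot be related to 6-week ultrasound damage

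*Protocol*

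**What the plan says.** Protocol section 5.3 (Study procedures) lists three steps for the 6-week visit: questionnaires, a physical examination and an ultrasound. Step 2 is "Physical exam by clinical neurophysiology research technician to evaluate dermatomas and subtle neurological injury". Step 3 is "Repeat ultrasound measurement of intercostal / subcostal nerve to assess nerve damage if neurological injury is present".

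Four other places describe the 6-week ultrasound and attach no condition to it:

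- Section 1 (Introduction and rationale): "after 6 weeks we want to repeat the ultrasound to see if nerve damage can be visualized at a later stage".
- Section 5.2 (Secondary study parameters/endpoints): "Postoperative ultrasound after 6 weeks with repeat measurements of intercostal and subcostal nerves".
- Section 8.3 (Benefits and risks assessment), as part of the burden on patients: "extra examinations (ultrasound, physical examination, questionnaire) after 6 weeks (estimated 20 minutes".
- The Summary, whose burden paragraph names the same examinations.

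The secondary objective in section 2 is "to correlate postoperative dullness, neuropathy, pain or muscle weakness to subcostal nerve damage on ultrasound, after 6 weeks". The Summary and section 5.2 repeat this correlation without a time point.

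Ultrasound is also performed during the operation session, before surgery and again after wound closure. The second of these is described as "Then repeat measurement of intercostal / subcostal nerve is performed to assess nerve damage / oedema", with no symptom condition. The study is "A explorative single-center prospective cohort study (n=25" patients).

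**The concern.** Step 3 is the instruction that staff will work from at the visit, so it is likely to decide which images exist. Read literally, it makes the scan depend on one of the two variables that the secondary objective wants to relate. This is partial verification: ultrasound status at 6 weeks is seen only where the examination is positive.

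At stake are three 6-week quantities: the association of neurological injury with ultrasound damage, the share of the cohort with ultrasound damage, and how often damage is visible in patients who have no injury. The third matters for interpretation, because if damage is common without injury, an image of damage says little about its consequences. This is a matter of data collection. A statistical analysis plan cannot supply a scan that was not taken.

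**Working it through.** The protocol gives no precision target, power or effect size for the 6-week scan, so there is no planned figure to reproduce. The check asks which cells of a two-by-two table are observed.

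**Step 1: cells observed if step 3 is followed.** Rows are injury at 6 weeks (yes, no); columns are ultrasound damage at 6 weeks (yes, no). Only the 'injury: yes' row is filled. The 'injury: no' row is empty by design, whatever the sample size.

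**Step 2: how many patients that may concern.** The Introduction gives 10% pain and 21% dullness, and no overlap. Either symptom therefore lies between 21% (full overlap) and 21% + 10% = 31% (no overlap). *Assumption:* this share equals the share with neurological injury at the 6-week examination. The protocol does not say so. The rates are patient-reported, described as temporary in part, and carry no time point.

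- At 21%: 25 × 0.21 = 5.25 scanned, 19.75 not scanned.
- At 31%: 25 × 0.31 = 7.75 scanned, 17.25 not scanned.
- If the examination found injury in only 10%: 25 × 0.10 = 2.5 scanned, and the chance that nobody is scanned is 0.90^25 = 7%.

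**Step 3: what the missing row does.** *Illustration with assumed counts:* 5 patients are scanned and 3 show damage (60%, exact 95% CI 15% to 95%). Let c of the 20 unscanned patients have damage. With a = 3, b = 2 and d = 20 − c,

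phi = (a·d − b·c) / √[(a+b)(c+d)(a+c)(b+d)].

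| c of 20 | phi | Difference in damage rate (3/5 − c/20) | Cohort incidence ((3+c)/25) |
|---|---|---|---|
| 0 | 60/√6600 = 0.74 | 60 points | 12% |
| 5 | 35/√13600 = 0.30 | 35 points | 32% |
| 10 | 10/√15600 = 0.08 | 10 points | 52% |
| 20 | −40/√4600 = −0.59 | −40 points | 92% |

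The observed data are identical in all four lines, so they cannot distinguish a strong positive association from a negative one.

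**Step 4: what remains estimable.** The scan after wound closure is unconditional, and the 6-week questionnaires and examination are unconditional. Damage on the immediate scan against 6-week symptoms therefore has both rows filled, in up to 25 patients.

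**Step 5: after the fix.** If all 25 are scanned, the 6-week table compares about 5 to 8 patients with about 17 to 20. The association becomes estimable but imprecise. As a guide to precision only, since the protocol states no test: with 5 against 20 patients and assumed damage rates, two-sided Fisher power at 0.05 is about 0.88 for 80% v 10% and 0.36 for 60% v 20%.

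**The case against.** A reader might infer that the secondary objective as a whole lacks a comparison group and cannot be estimated. The documents do not support that, for three reasons.

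- The immediate postoperative scan covers patients with and without later symptoms. In section 2 the time phrase may date the symptoms, the scan or both, and the Summary and section 5.2 give the correlation no time. A correlation of 6-week symptoms with immediate damage is one legitimate reading. The wording does lean towards the 6-week scan: section 2 places damage directly after surgery under the primary objective, and section 5.2 lists the later scan as a secondary parameter.
- The trigger is neurological injury, apparently as found at the step 2 examination, and no threshold is given. It is not the same as pain, dullness or weakness taken singly. Single symptoms could still vary among those scanned, but in a small, selected group.
- Step 3 is not the settled rule, because four other places omit the condition. Equally, none of those four says outright that every patient is scanned. The firm finding is the contradiction.

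It is also tempting to say that the result will be inflated, as in the line c = 0 above. That requires counting unscanned patients as undamaged, which the protocol nowhere proposes; section 7 plans counts and percentages only.

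Finally, this is a secondary objective in a small exploratory cohort, and precision stays modest after any repair. That stands and lowers the severity. It does not remove the need for one rule on who is scanned.

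**Conclusion.** The point holds as an internal contradiction with a defined consequence. Section 5.3 conditions the 6-week scan on neurological injury; the Summary and sections 1, 5.2 and 8.3 do not. Under the conditional rule, three quantities cannot be estimated: the association of neurological injury with 6-week ultrasound damage, the cohort's 6-week incidence of ultrasound damage, and the frequency of damage in patients without injury. This follows from the design and needs no assumed rate.

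The correlation of 6-week symptoms with damage on the immediate scan survives. The primary endpoints, which rest on the scans in the operating session and the trocar distances, are unaffected.

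The size (about 5 to 8 of 25 scanned, 17 to 20 not) rests on equating reported symptom rates with the share scanned, and the examination may find more or fewer injuries. The phi values are illustrations from assumed counts. Severity: should be fixed, ideally before the first 6-week visit, because missed scans cannot be recovered.

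**What to change.** Delete the conditional clause at the end of step 3 in section 5.3, so that all patients attending the 6-week visit are scanned. State that the 6-week incidence and the 6-week correlation are based on all patients scanned. This aligns step 3 with the Summary and sections 1, 5.2 and 8.3, and adds no procedure that the protocol does not already list.

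The cost is a short research scan for most patients at a visit they already attend. The declared time may need a small upward revision. Section 8.3 allows 20 minutes in total, and section 5.3 gives the 6-week questionnaires about 15 (the two items listed add to 10). That leaves 20 − 15 = 5 to 20 − 10 = 10 minutes for examination and scan together. Since the scan follows the examination, it would also help if the person scanning were unaware of its findings where staffing allows.

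If the sponsor prefers to keep the condition, three changes make the protocol coherent:

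- restrict the correlation objective to the immediate postoperative scan;
- report the 6-week scans descriptively, with the number scanned as denominator;
- state that unscanned patients are not counted as undamaged.

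In that case, the condition should also appear in the Summary and sections 1, 5.2 and 8.3, and neurological injury should be defined.

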# METHODS

## Main study parameter/endpoints

- To assess postoperative nerve damage on ultrasound.
  - - Pre- and postoperative ultrasound to identify and measure the intercostal and subcostal nerves (precise location and cross sectional area (CSA) measurement)
- To measure the distances of the subcostal nerve to trocar positions.
  - - Postoperative measurement of distances (in mm) to trocar positions after marking of the nerve

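### The scan before incision follows a procedure that marks the nerve on the skin, and no step hides that mark from a surgeon who is meant to be blinded to the scan

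*Protocol*

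**What the plan says.** All of the following is in the protocol.

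- **First scan.** Section 5.3, first intraoperative step: "After positioning in jack-knife position, an ultrasound is performed by a clinical neurophysiology research technician". The sentence continues "with measurement of the intercostal / subcostal nerve (see scan-protocol below", so this scan is to be done by the scan procedure given later in the section. The operation is the next step.
- **Scan procedure.** It includes "Cross sectional area (CSA) measurement of subcostal nerve, marking the position on skin", and then "Following lateral / medial cutaneous nerve branches in surgical area". One procedure is given, and it is not split into a version for before incision and a version for after closure.
- **Blinding.** The first intraoperative step also says that the "surgeon is blinded for the results of preoperative ultrasound measurements to reduce bias". The reason given is that the study is to judge the current technique. The third step extends the blinding to the scan after closure, to protect later operations.
- **Record.** At the first scan, "Nerve locations are captured with photography".
- **Endpoint.** Section 5.1 lists as a main endpoint "To measure the distances of the subcostal nerve to trocar positions". It describes a postoperative measurement in millimetres, taken once the nerve has been marked, and does not say at which scan the mark is made.
- **Data access.** Under data management, section 5.3 adds: "Other authors in this study can view the data upon request".

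**The concern.** The blinding exists so that the trocars go where the surgeon would normally put them. The part of the scan result that could change trocar placement is the location of the nerve, and a skin mark shows exactly that. If the mark is still there when the trocars go in, the surgeon has been given the information that the blinding was meant to withhold.

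The trocar-to-nerve distance is then at risk of describing placement made with knowledge of the nerve, and not the current technique. A surgeon who reacts to a visible nerve position would be expected to move away from it, so the study could make the current technique look safer than it is. This is a single cohort. No control group would show the shift, and no analysis could remove it afterwards.

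**Working it through.** The protocol derives no figure on this point, so there is nothing to reproduce. The check is to put its steps in order and compare them with what the blinding needs.

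**Order of events as written (section 5.3)**
1. The patient is placed in jack-knife position.
2. The technician scans by the scan procedure, which includes marking the nerve position on the skin. Locations are photographed.
3. The surgeon, said to be blinded to that scan, places the trocars and operates.
4. After wound closure the nerve is scanned again, the shortest distance from nerve to trocar sites is measured, and photographs are taken.

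**What the blinding needs.** Between events 2 and 3, the mark must be absent, removed or concealed. No sentence provides for any of these, and none keeps the surgeon from seeing the skin.

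**Two readings of the marking step**
- *Marked at the first scan.* This follows from the cross-reference in the first intraoperative step. The mark then precedes trocar placement, and the conflict with the blinding is direct unless it is hidden.
- *Marked only after closure.* Section 5.1 fits this reading, because it names marking together with the postoperative distance. There is then no conflict, but the scan procedure does not limit marking to that scan.

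The text does not decide between them. A technician who follows section 5.3 to the letter acts on the first reading.

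**Direction of the bias.** Let *p* be the proportion of patients in whom the surgeon sees the mark and reacts, and *δ* the mean shift in distance (mm) in those patients. Then

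expected mean distance = mean distance under current technique + *p* × *δ*.

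Avoidance makes *δ* positive, so the bias is upwards. It is zero if *p* = 0 and equals *δ* if *p* = 1 (all 25 patients). For nerve damage the path is longer. The introduction lists compression, entrapment or angulation, direct trauma and indirect trauma as mechanisms, and trocar position need not govern all of these. A downward bias in damage is possible but less direct.

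**Size.** The protocol gives neither *p* nor *δ*, no expected distance or spread, and no expected rate of damage on ultrasound. Its 10% (pain) and 21% (dullness) are symptom rates reported by the centre's earlier patients. They cannot stand in for ultrasound damage, so no size is calculated.

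**The case against.** The best defence is that the protocol plainly intends blinding and that its text allows a harmless procedure. Photographs at the first scan would let the mark be wiped off, and section 5.1 places marking with the postoperative measurement. The scan procedure can be read as a generic checklist for every scan, with marking relevant only after closure. The study is also exploratory, descriptive and small. Much of this stands: it shows that unblinding is not established. It does not remove the conflict, because the first scan is expressly sent to a procedure that marks the skin and nothing says that the mark is gone before the operation.

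A reader might infer more than the documents support:

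- **That the surgeon does see the mark.** No sentence says so. It is inferred from the absence of a removal or concealment step.
- **That both main endpoints would describe ultrasound-guided surgery.** The second intraoperative step calls for the usual technique. What is marked is the position of the subcostal nerve; abnormalities in the branches are noted against reference lines. Distance is plausibly affected, damage less directly.
- **That the data-access sentence breaks the blinding.** It gives no timing, the data listed with it are consent, questionnaires and medical records, and nothing says that an operating surgeon is one of the other authors. It is a small gap, not a breach.
- **That the loss can be put in numbers.** Any assumed damage rate or count of avoided injuries would have no source in the protocol.

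**Conclusion.** The concern holds as a conflict between instructions. The scan before incision follows a procedure that marks the nerve on the skin, no step hides the mark, and the surgeon is said to be blinded to that scan. Section 5.1 leaves open which scan is marked and does not resolve it.

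The consequence is conditional on two assumptions: that the mark is made before incision and remains visible at trocar placement, and that the surgeon reacts by moving away from it. Under both, the trocar-to-nerve distance is biased upwards and nerve damage possibly downwards, in anything from none to all of the 25 patients. The size is unknown. Because the design could neither reveal nor correct the bias later, this is more than a missing operational detail and should be settled in the protocol.

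**What to change.** Reconcile section 5.1 with the intraoperative steps and the scan procedure in section 5.3, by stating that:

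1. at the scan before incision, the nerve position is recorded by photograph and against the midaxillary and umbilical lines, which the scan procedure already uses to locate abnormalities;
2. any skin mark made at that scan is removed or concealed before the surgeon sees the field;
3. the mark used for the distance measurement is made at the scan after wound closure.

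As a minor addition, state that operating surgeons do not view scan data or photographs until the last patient has been operated on.

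The cost is a few sentences and very little time in theatre. There is one real downside. If the nerve cannot be seen after surgery, no fresh mark can be made, and the distance must be taken from the recorded preoperative position. Whether the nerve can be visualised around surgery is itself part of the primary objective, so this may happen. The photograph therefore needs a scale, the trocar sites should be recorded against the same lines, and distances obtained this way should be flagged in the data. None of this changes the operation.
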